### Sample size calculation

The sample size was calculated on the basis of the primary outcome, namely, the total operation time. Current reports on the “cross technique” for LESS-TH show that the average operation time is 170.1 ± 49.97 min [15]. According to our pilot retrospective study of 46 patients undergoing LESS-TH with the “chopstick technique,” the average operation time was 125.72 ± 51 min. The difference between the average values of the two operation time was determined as the minimum difference. A bilateral difference test was used. The first-order risk (*α*) is 0.05, and the power (1-β) is set at 0.9 for the study. Based on the evaluation of PASS 25.0 statistical software, each group requires 29 patients. The study consists of equivalent numbers for each treatment arm. In consideration of the loss to follow-up and multiple surgeons’ influences on the operation time, the sample size was expanded by 15% to 34 patients for each group. A total of 68 patients are required for the experiment.

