### Measurement and data collection

#### Outcome measures

The following baseline characteristics of patients will be documented: age, BMI, volume of the uterus, concomitant medications, EQ-5D scores, and anesthesiology scores (ASA).

B. The specific process for follow-up (Table 1):

During the screening period (before surgery), surgical indication, inclusion and exclusion indicators, gynecological check results will be investigated.

The collection of data on the day of surgery will include the successful removal of the uterus by the technique as randomized; conversion to laparoscopy or laparotomy; the total operation time (classified as the single-port establishment time, pelvic-abdominal adhesion release time, total hysterectomy time, specimen removal time, and stump suture time); estimated blood loss; intraoperative complications (including blood transfusion, vascular repair, bowel surgery, bladder surgery, ureter operation); and surgeon fatigue.

On the day of discharge, data on hospitalization expenses and the postoperative hospital stay will be collected by the research assessor.

During the 8 weeks after the intervention, postoperative complications (such as a second operation, infection, urogenital tract injury, intra-abdominal hemorrhage, incision hematoma, incision infection) will be recorded and rated by the Clavien–Dindo classification method. Health-related quality of life (EQ-5D) will be assessed again at 8 weeks (Table 2).

**Table 2 Tab2:** Patient’s characteristics and data collection

Timepoint	Study period							
	Enrollment	Allocation	Post-allocation					Close-out
		0	Pre-operation	Operation	Post-operation	Discharge	After 8 weeks	

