### Statistical analysis

The research assistants will send nonblinded data to a statistician for analysis, who will remain blinded to the other investigators until all data analysis is complete. The data will be analyzed with SPSS version 25.0 software. Continuous variables that are normally distributed will be analyzed according to the means and SDs, and discrete variables that are nonnormally distributed will be summarized as medians, ranges, and IQRs. The *T* test and nonparametric analysis will be applied to analyze continuous variables with normal and nonnormal distributions, respectively, and categorical variables will be analyzed by the *χ*
^2^ test or Fisher’s exact test. *P* < 0.05 will indicate a statistically significant difference.

If it is limited to a single missing item, the missing data will be estimated from the given mean values. Imputation will not be attempted if the missing data include the whole table or more than one item. A sensitivity analysis will be performed to determine whether the method used to deal with missing data is appropriate.

According to the analysis of 1534 laparoscopic total hysterectomies by the Netherlands prospective cohort study [17], the surgical time is influenced by the uterine weight and the methods of hysterectomy, and the independent risk factors for surgical conversion are body mass index (BMI), uterine weight, laparoscopic hysterectomy method, and age. The stratified randomization of uterine weight will be conducted. Moreover, the BMI and age subgroups will be evaluated.

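### Non-normal hospitalization expenses would ordinarily go to a rank test, which does not compare the average bill; a mean difference with a confidence interval would fit the economic objective better (optional to minor)

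*Protocol article*

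**What the plan says.** Under Secondary objectives, the protocol article names economic benefit, judged by the expenses of the hospital stay, as one of eight groups of secondary outcomes. Under Outcome measures, one amount per patient is recorded: "On the day of discharge, data on hospitalization expenses and the postoperative hospital stay will be collected by the research assessor".

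The Statistical analysis section sets a single rule for every continuous outcome. The t "test and nonparametric analysis will be applied to analyze continuous variables with normal and nonnormal distributions, respectively", and P < 0.05 "will indicate a statistically significant difference". The descriptive rule runs in parallel: "Continuous variables that are normally distributed will be analyzed according to the means and SDs", while "discrete variables that are nonnormally distributed will be summarized as medians, ranges, and IQRs". Expenses are not treated separately, and no comparison of mean expenses is given for the case where they are non-normal.

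Two points of wording matter:
- The text says nonparametric analysis and names no test. Beside a t test, the ordinary reading is a Mann-Whitney rank test.
- The sentence on medians refers literally to discrete variables. This looks like loose wording for non-normal continuous variables, because nothing else in the section says how those are summarized.

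**The concern.** An economic benefit is normally understood as money saved per patient treated. That is a statement about the arithmetic mean, because mean expense times number of patients gives the total bill. A rank test asks something else: whether a patient in one arm tends to have a lower bill than a patient in the other. It gives a very large bill little more weight than a moderately large one, and the median leaves the upper tail out.

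The non-normal branch is likely to apply. The protocol itself lists the events that produce large bills: conversion to multichannel laparoscopy or laparotomy, transfusion, vascular repair, and bowel, bladder or ureter surgery. It also makes conversion and complication rates secondary outcomes, so it allows that they may differ between arms. If a shorter operation trims the routine bill in the arm that has a few more costly cases, the rank test would register the trimming and largely miss the costly cases. A saving could then be reported although the average bill is the same.

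**Working it through.** **Sample size used.** The plan's own figure concerns operation time and is reproduced only to fix the number per arm.
- Difference: 170.1 − 125.72 = 44.38 min.
- Common SD: √((49.97² + 51²)/2) = 50.49 min.
- Two-sided α 0.05, power 0.90: the t-test solution is 28.19, so 29 per group, as stated.
- Expansion: 29 × 1.15 = 33.35, so 34 per group, as stated.

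**Cost model (all assumptions; the documents give no cost figures).** Routine costs are lognormal with log-SD s, the same in both arms. A fraction p of patients has a bill m times the routine one. Arm A has more costly cases than arm B. Means are equal when

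routine A / routine B = (1 + p_B(m − 1)) / (1 + p_A(m − 1)).

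| Costly cases, A vs B | m | Ratio | Routine cost lower in A by |
|---|---|---|---|
| 10% vs 5% | 2 | 1.05/1.10 = 0.955 | 4.5% |
| 10% vs 5% | 3 | 1.10/1.20 = 0.917 | 8.3% |
| 15% vs 5% | 2 | 1.05/1.15 = 0.913 | 8.7% |
| 15% vs 5% | 3 | 1.10/1.30 = 0.846 | 15.4% |

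**Why the spread of routine costs matters.** A rank test responds to P(A's bill is below B's), which is 0.5 under its null. Take 10% vs 5% and m = 3, where the log shift between routine bills is −ln 0.917 = 0.087.
- s = 0.15: P(routine A < routine B) = Φ(0.087/(0.15√2)) = 0.659. Overall: 0.90 × 0.95 × 0.659 + 0.90 × 0.05 × 1 + 0.10 × 0.95 × 0 + 0.10 × 0.05 × 0.659 = 0.61.
- s = 0.40: P(routine A < routine B) = Φ(0.087/(0.40√2)) = 0.561. Overall: 0.855 × 0.561 + 0.045 × 0.982 + 0.095 × 0.037 + 0.005 × 0.561 = 0.53.

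The means are equal in both cases, but the rank test has much more to detect in the first.

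**Simulation of the plan's rule.** There were 34 patients per arm, a two-sided test at 0.05, and 3,000 to 6,000 trials per setting. The plan names no normality check, so Shapiro-Wilk below 0.05 in either arm was taken to select the rank test, and a t test was used otherwise. Rejection rates with equal mean bills and 10% vs 5% costly cases, given as the spread over repeat runs:

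| log-SD | m = 2 | m = 3 |
|---|---|---|
| 0.15 | about 11% | 35% to 37% |
| 0.20 | 6% to 8% | 19% to 20% |
| 0.30 | 5% to 6% | 9% to 10% |
| 0.40 | about 5% | about 7% |

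- With 15% vs 5% costly cases, the rate runs from about 6% (m = 2, log-SD 0.30) to about 75% (m = 3, log-SD 0.15). These settings need the larger routine savings shown in the first table.
- With the same distribution in both arms, the rate is about 5%.
- A Welch test of means stays near 5% in all these settings.
- At log-SD 0.15 to 0.20, the normality check chose the rank test in 97% or more of trials. Nearly all rejections had the lower median in the arm with more costly cases.

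**A limit on the alternative.** Under more extreme shapes the Welch test drifts too. With tripled bills in 5% vs 0% of patients, it rejected in about 10% of trials and the rank test in about 29%.

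**The case against.** The strongest reply is that no sentence in the protocol sets out a mean-cost, budget-impact or cost-effectiveness hypothesis. Equality of means is a convention of health economics brought to the text. That is fair as far as it goes, but an economic benefit measured in expenses has no obvious meaning that leaves out the average bill.

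Nonparametric analysis could also cover a bootstrap comparison of means, and an unseen analysis plan might say so. This stands as a caveat. However, the protocol does state a rule that covers expenses, and it pairs non-normality with medians, so the plan would have to override the ordinary reading rather than fill a gap.

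The objection on size carries the most weight. Eligibility runs from fibroids to early cancers, ages 18 to 80, ASA 1 to 3 and any uterine size, so routine costs may well be more variable than a log-SD of 0.20. Most of the excess then disappears. The example also needs a higher rate of costly cases offset by just enough routine saving to equalize the means. The Harm section expects no specific added risk, and bills after discharge do not enter the measure. Conversions and complications are reported separately, so a reader would see them beside the expenses.

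A reader might infer that the chopstick arm will have more costly cases, or that the rule generally produces false savings. The documents support neither. They contain no cost data and no evidence of differing cost tails, and with equal distributions the test keeps its level.

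**Conclusion.** The mismatch holds: on its ordinary reading, the stated rule tests something other than average expense per patient, while the objective is economic. With equal mean bills, 34 per arm and costly cases in 10% vs 5% of patients, it would indicate a difference in anything from about 5% to about 37% of trials. The position in that range depends mainly on the spread of routine costs and on how expensive a costly case is. Both are assumptions, so neither the upper nor the lower end can be claimed for this trial. The high figures under 15% vs 5% rest on routine costs that are 9% to 15% lower, which is no longer a slight saving.

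The consequence is confined to the economic conclusion, one secondary outcome of a trial that describes itself as exploratory. It would be wrong to infer that the primary comparison of operation time, the sample size or the safety data are affected. Severity is optional to minor.

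**What to change.** Add one sentence to the Statistical analysis section: for hospitalization expenses, arithmetic means per arm and the mean difference will be reported with a Welch or bootstrap 95% confidence interval whatever the normality result, and the economic conclusion will rest on that interval. Keep the median and IQR as description. In the same edit, correct the word discrete in the sentence on medians if non-normal continuous variables are meant.

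No new data are needed. The price is a wider interval when a few bills are very large, which is the real uncertainty about average cost at this sample size. Adjustment for uterine-size stratum is a separate matter and is not needed here.

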### Randomization and blinding

In the study, stratified randomization will be adopted. Prior to randomization, all qualified participants will be classified according to uterine size by ultrasonic measurement (class A = uterine size smaller than 10 cm of the maximum diameter, class B = uterine size between 10 and 15 cm of the maximum diameter, and class C = uterine size larger than 15 cm of the maximum diameter), since uterine size is the primary determinant of the operation time for hysterectomy.

The research assistant will acquire a randomized timetable generated by a computer. Trial participants and research assessors will be blinded to the information of group allocation, as ensured by sequentially numbered, opaque and sealed envelopes. The research assistant will be excluded from the results evaluation and data collection. Patients will be blinded to distribution and intervention information. In case of serious adverse events, the outcome evaluator will inform the surgeon to evaluate whether it is related to the intervention and carry out further treatment without unblinding the patient.

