### Main research indicators and the control of confounding factors and bias

The criteria of a newly successful technology are easy to master, preferred by surgeons and ultimately benefiting patients. However, these evaluation indicators are more complicated, with some being subjective, and some are difficult to evaluate. At present, the superior indicator for the evaluation of surgical techniques is operation time, which is also an objective evaluation parameter for differences in surgical techniques. The reduction in operation time can also indirectly reflect the benefits to patients. Therefore, this study selected operation time as the primary endpoint and other indicators, such as the fatigue of surgeons, as secondary indicators.

The size of the uterus affects the difficulty of total hysterectomy, which is the main confounding factor of the influence of the surgical technique on the operation time. According to the size of the uterus, we set up a stratified grouping study to eliminate the influence of uterine size as a confounding factor of the study. The intraoperative separation of adhesions is another influencing factor of surgical difficulty and a major research indicator in LESS hysterectomy. The study excluded cases that may cause severe intraoperative adhesions and added surgical time classifications during the operation: the single-port establishment time, pelvic-abdominal adhesion release time, total hysterectomy time, specimen removal time, and stump suture time, which eliminated research bias.

This study limits the qualifications of surgeons to those who have mastered both technical methods and have completed more than 40 LESS operations, thereby overcoming the learning curve of the new technology. Surgical videos of each operation are retained, and these will be evaluated by the clinical trial data monitoring committee (DMC). Above all, the research results will have better validity and universality.

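### The primary comparison of operation time leaves out the uterine-size strata and lets a normality check choose the test, which costs precision and leaves the effect measure open

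*Protocol article*

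**What the plan says.** The primary outcome is total operation time, and the trial was sized on it: "The sample size was calculated on the basis of the primary outcome, namely, the total operation time" (Sample size calculation). The inputs are means and SDs in minutes. For the cross technique "the average operation time is 170.1 ± 49.97 min", and for the chopstick technique "the average operation time was 125.72 ± 51 min".

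Patients are classified before allocation into three classes of maximum uterine diameter on ultrasound, "since uterine size is the primary determinant of the operation time for hysterectomy" (Randomization and blinding). The Discussion relies on this design feature: "we set up a stratified grouping study to eliminate the influence of uterine size as a confounding factor of the study".

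The Statistical analysis section fixes one rule for every continuous variable, the primary outcome included: the T "test and nonparametric analysis will be applied to analyze continuous variables with normal and nonnormal distributions, respectively". Uterine size enters that section only through the statement that allocation is stratified (there by uterine weight). No stratum term, covariate adjustment or stratified test appears anywhere in the article.

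**The concern.** There are two separate problems.

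1. **Strata left out.** Stratifying the allocation makes the arms alike in uterine size. It does not take the variation between size classes out of the residual variance on which a two-sample t test bases its standard error. If size matters as much as the protocol says, the test treats explainable variation as noise and the confidence interval is wider than it needs to be. Under balanced allocation within strata, that standard error also overstates the true variability of the arm difference, so the test rejects less often than 5% under the null.

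2. **Test chosen from the data.** The trial is powered for a mean difference in minutes. If operation times fail a normality check, the rule switches to a nonparametric comparison, which does not estimate a mean difference in minutes. What the primary result measures is then settled only after the data are seen.

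**Working it through.** **Inputs from the protocol (Sample size calculation).** Means 170.1 and 125.72 min; SDs 49.97 and 51; two-sided alpha 0.05; power 0.90; 29 per arm, expanded to 34 (68 in total).

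**Inputs assumed, because the protocol gives none.** Share of variance explained by size class, R² = 0.1 to 0.4; stratum mix 50/35/15%; permuted blocks of 4 within strata; normal errors unless stated.

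**Step 1: reproduce the plan's figure.**
- Difference = 170.1 − 125.72 = 44.38 min.
- Pooled SD = √[(49.97² + 51²)/2] = 50.49 min. Standardized difference = 44.38/50.49 = 0.879.
- Noncentral t power is 0.898 at 28 per arm and 0.908 at 29 per arm, so 29 reproduces as an unadjusted two-sample t test. At 34 per arm the power is 0.946.

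**Step 2: standard error.**
- Unadjusted, 34 per arm: 50.49 × √(2/34) = 12.25 min.
- Adjusted for class, the SE shrinks by about √(1 − R²). At R² = 0.3 this is 12.25 × √0.7 = 10.24 min, 16% smaller. An unadjusted analysis would need about 68/0.7 = 97 patients for the same precision.

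**Step 3: type I error of the unadjusted t test (34 per arm).** With balance inside strata, the approximation is 2 × [1 − Φ(1.96/√(1 − R²))].

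| R² | Formula | Simulated, blocks of 4 | Stratum-adjusted, simulated |
|---|---|---|---|
| 0.1 | 0.039 | 0.039 | 0.048 |
| 0.2 | 0.028 | 0.030 | 0.049 |
| 0.3 | 0.019 | 0.020 to 0.024 | 0.052 |
| 0.4 | 0.011 | 0.011 | 0.051 |

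Blocks of 2 and 6 give much the same (0.038 to 0.042 at R² 0.1; 0.019 to 0.021 at R² 0.3). With simple randomization inside strata, the unadjusted test is about nominal (0.047 to 0.050).

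**Step 4: power, 34 per arm, blocks of 4.**

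| R² | 44.38 min: unadjusted / adjusted | 30 min (assumed): unadjusted / adjusted |
|---|---|---|
| 0.1 | 0.954 / 0.965 | 0.68 / 0.71 |
| 0.2 | 0.961 / 0.976 | 0.680 / 0.765 |
| 0.3 | 0.972 / 0.991 | 0.697 / 0.813 |
| 0.4 | 0.976 / 0.995 | 0.719 / 0.879 |

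The loss is 1 to 2 points at 44.38 min and about 4 to 16 points at 30 min.

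**Step 5: the normality rule.** Choosing between t test and rank test by a Shapiro-Wilk check barely changes type I error under normal errors (0.020 either way at R² 0.3). With lognormal errors at R² 0.3 and 29 per arm, the rule usually selects the rank test. Its power is then 0.98, against 0.96 for the stratum-adjusted model on raw minutes. The fault in the rule is therefore the undetermined effect measure; its effect on the error rate is negligible.

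**The case against.** The strongest defence is that nothing here makes the result invalid. The trial was sized for an unadjusted t test, that test keeps its planned power at the planned difference, and any distortion of the error rate is in the safe direction. This stands, and it limits the weight of the point. A reader might infer that the trial is underpowered or that false positives are inflated; the protocol's own figures support neither.

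A reader might also take it as settled that the error rate is off nominal. The article mentions stratified randomization and a computer-generated list but no blocks, and without blocking the unadjusted test is about nominal. The R² values are likewise assumed, and the 30-min difference is not in the protocol, which treats 44.38 min as the minimum difference. A smaller effect is still worth considering, since 44.38 min sets a published series against the centre's own 46 retrospective cases, which is not a randomized contrast.

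It can be said that an exploratory trial reported in a condensed article may leave covariate terms to an analysis plan. But the article does name the tests, and those tests do not match its design.

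Finally, with skewed times a rank test can beat a linear model on raw minutes, so the claim of lost power is clearest for near-normal times. This also stands and shapes the fix.

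Neighbouring matters do not belong to the core claim. The BMI and age subgroups ("Moreover, the BMI and age subgroups will be evaluated") follow a sentence about risk factors for conversion. How EQ-5D and expenses are analysed is secondary. Surgeon identity is not among the listed data items, so adjustment for surgeon cannot be assumed to be free.

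**Conclusion.** The point holds as an efficiency and prespecification issue. The named analysis ignores the stratification factor that the protocol itself calls the main determinant of the primary outcome. If that factor is prognostic, precision is lost whether or not blocks are used: at R² 0.3 the standard error is about 12.2 min where about 10.2 would do. Conservatism of the test (type I error of about 0.04 down to 0.01 for R² 0.1 to 0.4) arises only if allocation is blocked within strata. At 44.38 min the practical loss is 1 to 2 points of power, and it becomes material only if the true difference is well below that.

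The open effect measure does not depend on R² or blocking: as written, the data decide whether the primary result is a mean difference in minutes or a rank comparison.

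The change is worth making before analysis, but the planned analysis is not invalid without it.

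**What to change.** In the Statistical analysis section, name one primary analysis that no normality check can change: a linear model of total operation time in minutes on arm plus uterine-size class (the three classes used for randomization), reporting the adjusted mean difference with its 95% CI. Add a log-time model or a stratified rank test (van Elteren) as a prespecified sensitivity analysis for skewed times. State whether permuted blocks were used within strata.

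The cost is a few lines of text. Size class is fixed for every patient before randomization, so no new data and no extra patients are needed. The model spends two degrees of freedom and, if times are strongly skewed, may give up a little power to a rank test (0.96 against 0.98 in the case above). Because the statistician receives unblinded data, the wording should be settled before those data are handed over.

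### BMI and age subgroups are planned, but the named two-group tests cannot show effect modification; use interaction estimates and a covariate model

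*Protocol article*

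**What the plan says.** The last paragraph of Statistical analysis cites a large laparoscopic hysterectomy cohort. For operation time, the cohort is reported to show that "the surgical time is influenced by the uterine weight and the methods of hysterectomy". For conversion, it is reported that "the independent risk factors for surgical conversion are body mass index (BMI), uterine weight, laparoscopic hysterectomy method, and age". The plan then gives two responses: randomisation stratified on the uterus, and the sentence "Moreover, the BMI and age subgroups will be evaluated".

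Earlier in the same section, the methods named for continuous outcomes are the t test or a rank-type alternative ("test and nonparametric analysis will be applied to analyze continuous variables with normal and nonnormal distributions, respectively"). Categorical outcomes get chi-square or Fisher's exact test. One general rule follows: P below 0.05 "will indicate a statistically significant difference". No regression model, covariate adjustment or interaction test is named. Nothing says which outcome the subgroups concern, where they are cut or how they are compared. BMI and age are both listed as baseline data under Outcome measures.

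**The concern.** A subgroup evaluation asks whether the technique effect differs by BMI or age. The named tests compare two arms. Applied inside a subgroup, they say only whether that subgroup on its own crosses 0.05. Significance in one half and not in the other is not evidence that the effects differ, and with 68 patients such a split result is common even when the effect is the same everywhere. A reader could conclude that the chopstick technique helps only heavier or only younger women when the data show nothing of the kind.

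A lesser matter is that BMI and age are introduced as risk factors, but splitting the sample on them does not adjust the overall comparison for them. Any precision that adjustment would bring is not used.

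**Working it through.** **Inputs (Sample size calculation).** Cross technique: "the average operation time is 170.1 ± 49.97 min". Chopstick technique: "the average operation time was 125.72 ± 51 min". The target effect is the gap between them ("The difference between the average values of the two operation time was determined as the minimum difference"). The test is two-sided at 0.05 with power 0.90, and allocation is equal.

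- Difference: 170.1 − 125.72 = 44.38 min.
- Common SD: √[(49.97² + 51²)/2] = 50.49 min.
- Standardised difference: 44.38/50.49 = 0.879.

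**The plan's own figure.** With the noncentral t distribution, power is 0.898 at 28 per group and 0.908 at 29, so 29 is the smallest size that reaches 0.90. Then 29 × 1.15 = 33.35, rounded up to 34. The stated 29 and 34 are reproduced; the sample size is not at fault here.

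**Separate tests within subgroups.** Assume the same 44.38 min effect in both parts of a split and a t test at 0.05 in each part. With powers p₁ and p₂,

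P(exactly one significant) = p₁(1 − p₂) + p₂(1 − p₁).

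For a median split (17 per arm in each half), p₁ = p₂ = 0.70, giving 2 × 0.70 × 0.30 = 0.42. Cut-points are not given, so other splits of 34 per arm are shown:

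| Split | Per arm in each part | Power in each part | Exactly one significant |
|---|---|---|---|
| 50/50 | 17 / 17 | 0.70 / 0.70 | 0.42 |
| 60/40 | 20 / 14 | 0.77 / 0.61 | 0.44 |
| 70/30 | 24 / 10 | 0.85 / 0.46 | 0.53 |
| 80/20 | 27 / 7 | 0.89 / 0.33 | 0.63 |

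With 29 per arm the same four splits give 0.47 to 0.65.

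**Both factors together.** This was simulated (4,000 trials per scenario, 34 per arm, BMI and age independent of each other and of the outcome, each split at its median). An interaction test was run on the same data.

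| True effect, same in all patients | Exactly one half significant, one factor | At least one of two factors | Interaction test, one factor | Interaction test, either factor |
|---|---|---|---|---|
| 100% of plan | 0.42 | 0.58 | 0.05 | 0.10 |
| 75% of plan | 0.51 | 0.68 | 0.05 | 0.10 |
| 50% of plan | 0.36 | 0.51 | 0.05 | 0.10 |
| None | 0.10 | 0.18 | 0.05 | 0.10 |

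**What the interaction test can detect.** With half-splits, the SE of the difference between the two effects is 50.49 × √(4/17) = 24.5 min. Power for an interaction of 44.38 min is Φ(44.38/24.5 − 1.96) = Φ(−0.15), about 0.44. The interaction detectable with 80% power is 2.80 × 24.5 = 68.6 min.

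**What adjustment might gain.** The documents do not say how much of the variance in operation time the covariates explain. Assuming 5%, 10% or 20%, the SD becomes 50.49 × √(1 − R²). Whole-trial power at 34 per arm then rises from 0.946 to 0.956, 0.964 or 0.979.

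**The case against.** The strongest reply is that the protocol says only that the subgroups will be evaluated. It does not say that each will be tested separately, or that the 0.05 rule applies to them. Cut-points and subgroup methods are commonly left to an analysis plan, and none is shown here. This stands as far as it goes: separate testing is an inference, and the missing cut-points are not the point. What remains is that the section does list its between-group methods, and none of them can compare effects between subgroups.

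Two stronger readings are tempting and should not be made.

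- A reader might infer that the lack of adjustment leaves the treatment comparison confounded by BMI and age. Randomisation prevents systematic bias; what is left is chance imbalance and some lost precision. The Discussion does speak of controlling confounding factors, but where it explains this it names uterine size, adhesions and surgeon experience, not BMI or age.
- A reader might infer that BMI and age are established predictors of the primary outcome. The section ties them to conversion, a secondary outcome. For operation time it names uterine weight and hysterectomy method. If the subgroup sentence is meant for conversion, the figures computed here for operation time do not carry over.

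It is also fair to say that the trial is labelled exploratory. That lowers the stakes, but it does not stop a subgroup P value from being misread.

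**Conclusion.** The point holds in a limited form. The named tests cannot assess effect modification. If they are used within subgroups, a result significant in one part only is likely by chance: about 42% per factor at the planned effect with a median split (up to 63% with an 80/20 split), and about 58% for at least one of BMI and age. An interaction test gives about 5% and 10%. These figures rest on assumed splits, separate t tests at 0.05, total operation time as the outcome, independent factors, and an effect that is the same in all patients. With no effect at all they fall to about 10% and 18%.

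The loss from not adjusting is one of precision only. It is probably small for BMI and age, whose link to operation time the documents do not show. The primary comparison remains valid. This is an inexpensive improvement to the wording, not a flaw that threatens the trial.

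**What to change.** Replace the subgroup sentence with wording to this effect:

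- Total operation time is analysed with a prespecified model containing treatment group, uterine-size class (the randomisation stratum), and BMI and age as continuous covariates.
- Effect modification is assessed only through a group-by-BMI and a group-by-age interaction, each reported as an estimate with a 95% CI and labelled exploratory.
- Within-subgroup P values are not used to claim that an effect is present or absent.

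The revised text should also say how this model relates to the present choice between a t test and a nonparametric test.

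The cost is a few model terms (two for size class, one each for BMI and age, and one for each interaction) and the loss of subgroup significance claims. Both covariates are already collected, so no patients, visits or measurements are added. The interaction test is weak at this sample size (about 44% power for an interaction as large as the whole planned effect), so it should be read as an estimate and not as a decision rule.
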